## **9. SUBGROUP ANALYSES**

In this study, patients with different backgrounds are expected to receive the treatment. For this reason, subgroup analyses for diabetes, multiple branch lesions, etc. will be performed, as well as the analysis including all the patients.

### **9.1 Pre-specified Subgroup**

#### **Patient units:**

- Diabetes
- Insulin-treated diabetes
- Age (  $\geq 75$  /  $< 75$  )
- Hemodialysis
- e-GFR  $< 30$ , Non-HD
- Oral anticoagulants

- History of hemorrhagic
- STEMI
- ACS
- Emergency procedure
- LMCA
- 2 vessel PCI
- 3 vessel PCI
- Total stent length category
- On-label/off-label

**Lesion units:**

- Bifurcation
- LMCA
- Multiple overlapping stent
- ISR of BMS and DES
- CTO
- STEMI
- ACS
- Emergency procedure
- Ostial RCA
- Small Vessel

**Notes: definition of lesions**

- Overlapping stent is dealt with as 1 lesion.
- When a stent is implanted in the left anterior descending coronary artery overlapped on another stent implanted for the left main coronary artery stenosis, these are considered to be two lesions in the left main coronary artery and in the left anterior descending coronary artery, respectively.
- Ostial lesion of the left anterior descending coronary artery that is not accompanied by significant stenosis in the left main coronary artery, but was stented from the left main trunk crossing over a circumflex branch, this is dealt with as one lesion at the ostium of the left anterior descending coronary artery instead of a left main trunk lesion.
- Bifurcation lesion is considered to be one lesion together with the side branch.
- Any lesion having a side branch of  $\geq 2.2$  mm in diameter by visual evaluation is defined as a bifurcation lesion.
- Any lesion localized within 3 mm from the ostium is defined as an ostial lesion.
- On-label lesion is defined as a lesion of  $\leq 30$  mm in length and 2.5-3.5 mm in lumen that has not been treated before. However, lesions responsible for a recent myocardial infarction, ostial lesions, bifurcation lesions, thrombotic lesions and highly calcified lesions are not defined as on-label lesions.
- Any lesion that does not meet the criteria for on-label lesion is defined as an off-label lesion.

## **10. OTHER NECESSARY ISSUES**

### **10.1 Ethical concerns/Obtainment of informed consent**

### **10.1.1 Protection of patients' rights**

Compliance with the Declaration of Helsinki

Study investigators should carry out this study according to either of “the latest version of the Declaration of Helsinki” or “Ethical Guidelines for Clinical Studies (Public Notice of the Ministry of Health, Labor, and Welfare No. 255, amended on July 30, 2008)” that maximizes the protection of patients.

### **10.1.2 Explanation to the patient**

Prior to enrollment, the investigator should give the patient the information document approved by the Ethics Committee (Attachment-9) with verbal explanation of details of the content. After the explanation, the consent form (Attachment-10) attached to the information document should be filled in with required data and be signed. The consent form completed with all required data should be duplicated in two copies. One copy will be kept by the patient, and another copy by the investigator. The original copy will be stored in the clinical chart.

### **10.1.3 Privacy Issues**

The clinical record, test data, records regarding the patient's informed consent, etc. will be stored at each medical institute, and the Case Report Forms and other related documents will be stored by the Data Center of the Department of Cardiovascular Medicine, Kyoto University. These records will be disclosed when requested for audit, but the confidentiality will be protected. Moreover, these records should be stored so as to be retrieved when necessary.

All the staff involved in this study has the duty of confidentiality as data handlers and should have the maximum efforts to protect patients' personal information. When patients' personal information is provided to outside of the institute, the name of each patient will be converted in initials at each institute, so that the patient can be identified only by the responsible person of the institute. Therefore, the name of the subject will not be transmitted from the participating institute to the Central Administration Office and the Data Center. Moreover, while the number assigned to the patient on the clinical chart at each institute will be used as the Patient ID Number, this number will be automatically encrypted when entered on the web. Therefore, the patient's number on the clinical chart is not transmitted from the participating institute to the Central Administration Office and the Data Center.

For identification of the patient and inquiry to each institute, the encrypted patient ID number and the patient's initials will be used. With regard to the use of the patient's initials as an ID data in this study, the risk of leaking personal information through the patient's initials only is considered to be very low. If the patient's initials are not used, identification of the patient should totally depend on the personal information control system of the institute. For this reason, investigation itself probably cannot be implemented, because identification of the patient will be impossible.

### **10.1.4 Compensation for health damages**

Compensation for health damages associated with this study will be done only when it is obligated by legal liability. Compensation for health damages, which is caused by the medical intervention itself and not associated with the clinical study, will be deliberated by each institute. Since the risk of health damages associated with this clinical study is expected to be very low, the Study Administration Office does not affiliate with any liability insurance.

### **10.1.5 Handling of treatment costs**

All the examinations and treatments regarding this study will be basically within the range of daily clinical practice. Therefore, medical fees of the patients participating in the study are refunded by medical insurances. For some blood tests and imaging tests that are not covered by medical insurances will be refunded from the research funds.

## **10.2 Protocol Approval**

This study will be carried out after examination and approval of the protocol by the Ethics Committee of each participating institute or equivalent organizations.

## **10.3 Protocol Amendments**

If amendments of the protocol are required after implementation of the protocol, this should be communicated from the Central Administration Office to each institute interrupting the study. After the amended protocol is examined, the results of examination will be submitted to the Ethics Committee of each participating institute for its approval.

## **10.4 Discontinuation and Completion of the Study**

In principle, the study will be continued until the target sample size is achieved at enrollment, and evaluation of all the patients completed. However, if adverse events clearly related with this study occurred, an independent Safety Evaluation Committee will discuss about the continuation of the study.

## **10.5 Discontinuation of the Study**

If this study must be discontinued for a reason that occurred during the study, the principal investigator, after discussing with study managers, should promptly report the discontinuation of the study and its reason to the Ethics Committee of each institute by written form.

## **10.6 Termination of the Study**

When enrollment of all the patients is completed, the principal investigator should notify the completion of enrollment to the investigator of each institute, and each institute terminates the enrollment. Moreover, when the completion of follow-up of all the patients is verified, the principal investigator should notify the completion of follow-up of the patients to the investigator of each institute. The investigator of each institute should submit the study completion report to the chief of the medical research group of affiliation.

## **10.7 Definitive Rating of Endpoints**

### **10.7.1 Clinical Endpoints - Clinical Events Committee (CEC)**

Clinical Events Committee (CEC) will carry out the definitive rating of all the clinical endpoints, and vascular and hemorrhagic adverse events.

### 10.7.2 Angiography Core Laboratory

Angiographic endpoints (pathological findings and qualitative analysis) will be rated by Angiography Core Laboratory.

## 11. Definition of Endpoints

### 11.1 Death

Death is defined based on the Academic Research Consortium (ARC) classification

- **Cardiac Death**  
Any death due to proximate cardiac cause (eg, myocardial infarction, low-output failure, fatal arrhythmia), unwitnessed death and death of unknown cause, and all procedure-related deaths, including those related to concomitant treatment, will be classified as cardiac death. In addition, any unexpected death even in patients with coexisting highly lethal disease (e.g., cancer) should be classified as cardiac, unless an unequivocal noncardiac cause can be established.
- **Vascular Death**  
Death caused by noncoronary vascular causes, such as cerebrovascular disease, pulmonary embolism, ruptured aortic aneurysm, dissecting aneurysm, or other vascular diseases.
- **Non-cardiovascular Death**  
Any death not meeting the criteria for cardiac death or vascular death, such as death caused by infection, malignancy, sepsis, pulmonary causes, accident, suicide, or trauma.

### 11.2 Myocardial Infarction: MI

Myocardial Infarction (MI) is defined by the ARC criteria. However, periprocedural MI will be evaluated by CKMB, because the evaluation by troponin is too sensitive.

- **Baseline MI evaluation**  
EEG showing ST elevation, development of new abnormal Q-wave, clinical symptoms specific to MI, troponin or CK-MB values exceeding the standard values
- **Periprocedural MI**
  - Occurrence of any of the following events within 48 hours after PCI procedure will be judged as MI.
    - CK-MB  $\geq 3$  times Upper Reference Limit (URL) (CK-MB value exceeding URL before procedure is not considered as a new MI, but as MI at enrollment.)
    - Abnormal ECG (new Q-wave, left bundle branch block)
  - Occurrence of troponin  $\geq 5$  times URL or CK-MB  $\geq 5$  times URL within 72 hours after CABG procedure accompanied by any of the following criteria will be judged as

MI. (CK-MB value exceeding URL before procedure is not considered as a new MI, but as MI at enrollment.)

- Abnormal ECG (new Q-wave, left bundle branch block)
- New occlusion of coronary autografts or grafts
- Reduction in living myocardium confirmed by diagnostic imaging
- **Spontaneous MI**
  - Occurrence of any of the following events at > 48 hours after PCI or > 72 hours after CABG will be judged as MI. MI caused by revascularization procedures, such as TLR and TVR, is defined as periprocedural MI.
  - Abnormal ECG (new Q-wave, left bundle branch block)
  - Troponin or CK-MB value > **URL** (CK-MB value exceeding URL before procedure is not considered as a new MI, but as MI at enrollment.)
- **Sudden Death**
  - When death occurred before blood sampling for biomarker measurements or while biomarkers appeared to be increasing, MI will be judged according to the following criteria:
    - Clinical symptoms suggesting ischemia that are accompanied by one of the following:
      - New ST elevation or left bundle branch block
      - Thrombus determined by angiography or at autopsy
- **Reinfarction**
  - When after onset of MI stable or decreasing values are confirmed in 2 biomarker measurements, but 20% increase 3 to 6 hours is observed after the second measurement.
  - If biomarkers are increasing or have not yet reached the peak, data are insufficient to diagnose reinfarction.

#### **Electrocardiographic Classification:**

- **Classification based on Q-wave**
  - **Q-wave MI (QMI)**
    - Development of abnormal Q-waves confirmed in 2 or more contiguous leads with or without elevation in cardiac enzymes.
  - **Non-Q-wave MI (NQMI)**
    - All MIs not classified as Q-wave.
- **Classification based on ST segment.**
  - **ST-elevation myocardial infarction (MI) (STEMI)**
    - New or presumably new elevation of ST segment at J point in 2 or more contiguous leads. Cut-off point is  $\geq 0.2$  mV in V1, V2 and V3 leads and  $\geq 0.1$  mV in other leads.
  - **Non-ST elevation myocardial infarction (MI) (NSTEMI)**
    - MI that is not STEMI

## 11.3 Coronary Revascularization

### Classification:

- **Target Lesion Revascularization (TLR)**  
PCI performed in the target lesion (within 5 mm of the stent edges), or CABG performed for restenosis of the target lesion or for treatment of other complications
- **Target Vessel Revascularization (TVR)**  
PCI performed in the target vessel or revascularization by CABG, including TLR
- **Target Vessel Revascularization-Remote (TVR-Remote)**  
Revascularization of a non-target lesion in the target vessel
- **Non Target Vessel Revascularization (Non-TVR)**  
Any revascularization in a vessel other than the target vessel
- **Non Target Lesion Revascularization (Non-TLR)**  
Any revascularization in a lesion other than the target lesion  
 $\text{Non-TLR} = \text{TVR-Remote} + \text{Non-TVR}$

### Clinically indicated coronary revascularization:

- The revascularization that meets the following criteria is considered as clinically indicated revascularization. Presence/absence of clinical findings is judged by the operator of the procedure before the revascularization.
  - Recurrence of angina pectoris, presumably related to the target vessel;
  - Objective signs of ischemia at rest or during exercise test (or equivalent), presumably related to the target vessel;
  - Signs of functional ischemia revealed by any invasive diagnostic test (e.g., Doppler flow velocity reserve [FVR], fractional flow reserve [FFR]);
  - Revascularization for  $\geq 70\%$  diameter stenosis even in the absence of the above-mentioned ischemic signs or symptoms.

## 11.4 Stent Thrombosis

Based on the ARC definition, Stent thrombosis is classified into definite, probable and possible according to the “probability”, and into acute, subacute late and very late according to timing of the onset.

- **Definite Stent Thrombosis**
  - Angiographic confirmation of stent thrombosis\*:
    - The presence of a thrombus† that originates in the stent segment (including 5 mm of the stent edges) is revealed by angiography, and presence of at least one of the following criteria within a 48-hour time window is observed:
      - Acute onset of ischemic symptoms at rest
      - New ECG changes that suggest acute ischemia
      - Typical rise and fall in cardiac biomarkers (refer to definition of spontaneous MI)

- Nonocclusive thrombus
    - Intracoronary thrombus is defined as a (spheric, ovoid, or irregular) noncalcified filling defect or lucency surrounded by contrast material (on 3 sides or within a coronary stenosis) seen in multiple projections, or persistence of contrast material within the lumen, or a visible embolization
  - Occlusive thrombus
    - TIMI 0 or TIMI 1 intrastent or proximal to a stent up to the most adjacent downstream side branch or main branch
  - Pathological confirmation of stent thrombosis:
    - Evidence of recent thrombus within the stent determined at autopsy or via examination of tissue retrieved following thrombectomy
  - **Probable Stent Thrombosis**
    - When the following cases occurred after intracoronary stenting:
      - Any unexplained death within the first 30 days after procedure†
      - Irrespective of the time after the index procedure, any MI in the territory of the implanted stent in the absence of any other obvious cause such as angiography or other lesions
  - **Possible Stent Thrombosis**
    - Any unexplained death from 30 days after intracoronary stenting
- \* The incidental angiographic documentation of stent occlusion in the absence of clinical signs is not considered to be a confirmed stent thrombosis (silent occlusion)
- † Intracoronary thrombus
- **Acute Stent Thrombosis**  
0-24 hours post stent implantation (Time 0 is defined as the time of removal of the guiding catheter).
  - **Subacute Stent Thrombosis**  
> 24 hours-30 days post stent implantation
  - **Late Stent Thrombosis \***  
> 30 days-1 year post stent implantation
  - **Very Late Stent Thrombosis \***  
> 1 year post stent implantation
- \* Including “primary” as well as “secondary” stent thrombosis after stented segment revascularization.

## 11.5 Surgery

- Including endoscopic surgeries and therapies
- Including CABG

- Excluding percutaneous intravascular treatments
- Including aortic aneurysm stent graft procedure
- Excluding tooth extraction

## 11.6 Bleeding/Hemorrhagic Complications

Bleeding/Hemorrhagic Complications will be evaluated using the TIMI, GUSTO and BARC definitions (References 22-24).

### **TIMI bleeding classification:**

Bleeding is classified by the Thrombosis in Myocardial Infarction (TIMI). Measurement of hemoglobin and hematocrit values at baseline is required for the severity rating.

- **Major Bleeding**
  - When any of the following criteria is met.
    - Intracranial hemorrhage
    - Decrease in hemoglobin to  $\geq 5$  g/dL decrease in the hemoglobin concentration
    - Absolute drop in hematocrit to  $\geq 15\%$  (Baseline – Onset of the event)
- **Minor Bleeding**
  - When blood loss is observed, and any of the following criteria is met:
    - Decrease in hemoglobin to  $\geq 3$  g/dL
    - Decrease in hematocrit to  $\geq 10\%$  (Baseline – Onset of the event)
  - When no blood loss is observed, but any of the following criteria is met:
    - Decrease in hemoglobin to  $\geq 4$  g/dL
    - Decrease in hematocrit to  $\geq 12\%$  (Baseline – Onset of the event)
- **Minimal Bleeding**
  - Any clinically overt sign of hemorrhage that is associated with a fall in hemoglobin to  $< 3$  g/dL.  
(Microscopical urine occult blood and fecal occult blood are not defined as Minimal bleeding.)

### **GUSTO bleeding classification:**

#### **Severe Bleeding**

- Life-threatening bleeding
- Intracranial hemorrhage
- Hemorrhage or bleeding that causes drop in blood pressure and requires interventions, such as infusion, blood transfusion, administration of a hypertensor, surgical interception.

#### **Moderate Bleeding**

- Bleeding that requires blood transfusion but does not meet criteria for severe bleeding

### **BARC bleeding classification:**

Bleeding is classified based on definitions by the Bleeding Academic Research Consortium (BARC). Measurement of hemoglobin concentration is required for severity rating.

- **Type 0:** No bleeding

- **Type 1:** Bleeding that is not medically significant and does not cause the patient to seek unscheduled performance of studies, hospitalization, or treatment by a health care professional.
- **Type 2 :** Any overt sign of haemorrhage that should be treated and does not fit the criteria for Types 3, 4, or 5, but does meet at least one of the following criteria:  
(1) requiring non-surgical, medical intervention by a health care professional, (2) leading to hospitalization or increased level of care, (3) prompting evaluation.
- **Type 3 :**
  - Type 3a
    - Overt bleeding plus hemoglobin drop of 3-5 g/dL
    - Transfusion with overt bleeding
  - Type 3b
    - Overt bleeding plus hemoglobin drop of  $\geq 5$  g/dL
    - Cardiac tamponade
    - Bleeding requiring surgical intervention (excluding dental/nasal/skin/haemorrhoid)
    - Bleeding requiring intravenous vasoactive drugs
  - Type 3c
    - Intracranial hemorrhage
    - Intraocular bleeding compromising vision
- **Type4:** CABG-related bleeding
  - Perioperative intracranial hemorrhage within 48 hours
  - Reoperation following closure of sternotomy for the purpose of controlling bleeding
  - Transfusion of  $\geq 5$  units of whole blood or concentrated red blood cell within 48 hours
  - Chest tube output  $\geq 2$  L within 48 hours
- **Type5:** Fatal bleeding
  - Type 5a  
Probable Fatal bleeding: no autopsy or imaging confirmation, but clinically suspicious
  - Type 5b  
Definite fatal bleeding: overt bleeding or autopsy or imaging confirmation

## 11.7 Composite endpoint

The following categories are defined as composite endpoint:

- **Target Lesion Failure (TLF)**  
Cardiac death, myocardial infarction (MI) of target vessels, Clinically indicated target lesion revascularization
- **Tagert Vessel Failure (TVF)**  
Cardiac death, myocardial infarction (MI), Clinically indicated target vessel revascularization
- **Major Adverse Cardiac Events (MACE)**  
Cardiac death, myocardial infarction (MI), Clinically indicated target lesion revascularization

## 11.8 Stroke or Cerebrovascular Accident

Acute onset of a neurological deficit that persists for at least 24 hours and is the result of a disturbance of the cerebral circulation due to ischemia or hemorrhage.

Deficits that last  $\leq$  24 hours are due to transient ischemic neurological attack and are not classified in this category.

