#### 8. Stroke

Presence/absence of stroke, date of onset, classification of stroke, lethality

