## **7. ENDPOINTS**

### **7.1 Primary endpoint**

The primary endpoint in this study is a composite endpoint of cardiovascular death in 12 months, myocardial infarction (MI), stroke (ischemic and hemorrhagic), stent thrombosis (Definite stent thrombosis [ST] not resulting in MI) and serious bleeding (TIMI Major/Minor).

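### The stroke definition in Section 11.8 leaves out strokes fatal within 24 hours and brief hemorrhagic deficits, and contradicts itself at exactly 24 hours; the loss falls on secondary stroke counts, not on the primary composite

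*Protocol*

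**What the plan says.** Section 11.8 sets two conditions for stroke. The first is duration: "Acute onset of a neurological deficit that persists for at least 24 hours". The second is mechanism: the deficit "is the result of a disturbance of the cerebral circulation due to ischemia or hemorrhage". The next sentence disposes of the rest: deficits lasting no more than "24 hours are due to transient ischemic neurological attack and are not classified in this category". No exception is made for death or for hemorrhage.

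Stroke appears in three places among the endpoints:

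- It is part of the primary composite in 7.1: "myocardial infarction (MI), stroke (ischemic and hemorrhagic), stent thrombosis (Definite stent thrombosis [ST] not resulting in MI) and serious bleeding (TIMI Major/Minor").
- It is part of the first major secondary endpoint in 7.2.1 (cardiovascular death, MI, stroke or definite ST).
- It stands alone in the secondary list in 7.2.2.

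The 12-month form (6.2.2, item 8) collects "Presence/absence of stroke, date of onset, classification of stroke, lethality".

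Two other definitions touch the same events. Vascular death in 11.1 is "Death caused by noncoronary vascular causes, such as cerebrovascular disease", among other causes. TIMI Major bleeding in 11.6 lists "Intracranial hemorrhage" as sufficient by itself, with no duration condition.

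**The concern.** A duration rule works for deficits that resolve. It fails when the patient dies first, because a deficit cannot be shown to last 24 hours in someone who died at hour 10. Applied as written, the most severe strokes fall into the category meant for the mildest events.

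The rule also covers hemorrhage in its first sentence but labels every short deficit as transient ischemic in its second. A brief hemorrhagic deficit is therefore misnamed by definition, although 7.1 counts hemorrhagic stroke explicitly.

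Finally, one sentence includes 24 hours and the other excludes it.

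What is at stake is whether the reported stroke count means what a reader will take it to mean. In a study of shortened antiplatelet treatment, ischemic and hemorrhagic strokes are both of direct interest.

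**Working it through.** **The plan's own figure.** The definition carries no number. The sample size in 8.1 is the only figure in the neighborhood, and it reproduces. The inputs are n = 1455, goal 6.6%, assumed rate 4.4%, one-sided alpha 0.025 and an exact binomial test.

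- Largest c with P(X ≤ c | 1455, 0.066) ≤ 0.025: c = 77, which is 77/1455 = 5.29%.
- Exact alpha: P(X ≤ 77 | 1455, 0.066) = 0.0225.
- Power: P(X ≤ 77 | 1455, 0.044) = 95.4%, against the stated 95% or so.
- Weight of a single event: 1/1455 = 0.069 percentage points.

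**Tracing cases through the definitions.** Non-cardiovascular death in 11.1 is whatever is neither cardiac nor vascular, so a vascular death is a cardiovascular death. With that, each kind of case can be followed into each endpoint:

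| Case | Stroke under 11.8 | Primary composite (7.1) | First major secondary (7.2.1) | Bleeding major secondary (7.2.1) | Stroke alone (7.2.2) |
|---|---|---|---|---|---|
| Ischemic stroke, death at 10 h | No | Counted, vascular death | Counted, vascular death | Not applicable | Lost |
| Intracranial hemorrhage, death at 10 h | No | Counted, vascular death and TIMI Major | Counted, vascular death | Counted | Lost |
| Intracranial hemorrhage, non-fatal, deficit clears at 12 h | No, labelled transient ischemic | Counted, TIMI Major | Lost | Counted | Lost |
| Non-fatal ischemic deficit of exactly 24 h | Yes and no | Unsettled | Unsettled | Not applicable | Unsettled |
| Non-fatal ischemic deficit that clears at 12 h after treatment | No | Not counted | Not counted | Not applicable | Not counted |

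**Reading the table.**

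- The first three rows never leave the primary composite. All three leave the separate stroke endpoint.
- Only the third also leaves the first major secondary endpoint, because that endpoint has no bleeding component to catch it.
- The fourth row is a plain contradiction between two sentences. It is the only one of the first four rows whose primary status is open, and it needs a duration of exactly 24 hours. Duration is not among the items listed in 6.2.2.
- The last row follows consistently from a duration-based definition. It is not an internal error.

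**Size.** The protocol gives neither a stroke rate nor the share of strokes that are fatal or resolved within 24 hours. The number of cases lost cannot be computed from it.

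**The case against.** The case against making much of this is good, and most of it stands.

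- **Early deaths.** The label in 11.8 is transient, and a deficit still present at death has not passed. The Clinical Events Committee gives the definitive rating (10.7.1) and would probably call such a case a stroke. The lethality item in 6.2.2 fits strokes fatal after 24 hours, so it does not prove that early deaths were in mind; it shows only that fatal strokes belong in the category. All this is fair, but the committee would be departing from the written rule, which states the duration condition without exception.
- **Cerebral hemorrhage as a harm of prolonged treatment.** Section 2 names it as a bleeding complication, and it is counted as bleeding under TIMI, GUSTO and BARC. That harm is therefore not lost from the study. This stands: the defect concerns the stroke counts only.
- **Bias toward the goal.** A reader might infer that treated ischemic strokes clearing within 24 hours are hidden and that this makes the 6.6% goal easier to meet. With the goal held fixed and a true rate of 6.6%, hiding 0.1 or 0.2 percentage points (assumed values) would raise the chance of passing, P(X ≤ 77 | 1455, 0.066 − d), from 2.25% to 3.2% or 4.4%. But the goal is built from the RESET rate of 4%, and the protocol does not say how RESET defined stroke. If RESET used the same rule, the benchmark omits the same events. The calculation assumes the bias that it would need to show.
- **Imaging or reperfusion criteria.** A reader might also infer that leaving them out is an error. It is a choice between definitions. Adding them in this study alone could break comparability with RESET, both for the goal and for the complementary Cox analysis in 8.1.

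**Conclusion.** The wording of 11.8 is defective in three ways: it has no provision for death within 24 hours, it labels brief hemorrhagic deficits as ischemic, and it overlaps at exactly 24 hours. The consequence is a possible undercount in the separate stroke endpoint and, for brief non-fatal hemorrhages only, in the first major secondary endpoint.

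The primary composite is essentially unaffected, because the early fatal and hemorrhagic cases enter it through 11.1 or 11.6. The test against 6.6% is not shown to be biased in either direction.

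This is a minor point, worth correcting because the correction is so cheap. It rests on a literal reading of 11.8 and on the absence of any other stroke rule in the protocol. The number of events cannot be given.

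**What to change.** Reword 11.8 in three places:

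1. After the 24-hour minimum, add: *or leads to death within 24 hours*.
2. Limit the exclusion to *ischemic deficits that resolve in less than 24 hours*. This removes both the overlap and the ischemic label on hemorrhages.
3. State that intracranial hemorrhage with a neurological deficit is stroke whatever its duration.

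Put the same text in the Clinical Events Committee's instructions. Ask the committee to compare the stroke item with deaths from cerebrovascular causes and with bleeds at an intracranial site. Cause of death, site of hemorrhage, stroke classification and lethality are already collected under 6.2.2. Once early deaths count, the exact hour of death no longer matters.

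Do not add an imaging or reperfusion clause unless RESET used the same rule. If such cases are of interest, report them only as a sensitivity count. Section 6.2.2 lists no imaging, treatment or duration item for stroke, so that count would need source records.

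The cost is a short text change and possibly a few more events in the secondary stroke counts. The primary comparison with RESET is essentially untouched, since the early fatal and hemorrhagic cases are already in the composite.
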